# Study of Mental Activity and Regular Training (SMART) in at risk individuals: A randomised double blind, sham controlled, longitudinal trial

**DOI:** 10.1186/1471-2318-11-19

**Published:** 2011-04-21

## Abstract

**Background:**

The extent to which mental and physical exercise may slow cognitive decline in adults with early signs of cognitive impairment is unknown. This article provides the rationale and methodology of the first trial to investigate the isolated and combined effects of cognitive training (CT) and progressive resistance training (PRT) on general cognitive function and functional independence in older adults with early cognitive impairment: Study of Mental and Regular Training (SMART). Our secondary aim is to quantify the differential adaptations to these interventions in terms of brain morphology and function, cardiovascular and metabolic function, exercise capacity, psychological state and body composition, to identify the potential mechanisms of benefit and broader health status effects.

**Methods:**

SMART is a double-blind randomized, double sham-controlled trial. One hundred and thirty-two community-dwelling volunteers will be recruited. Primary inclusion criteria are: at risk for cognitive decline as defined by neuropsychology assessment, low physical activity levels, stable disease, and age over 55 years. The two active interventions are computerized CT and whole body, high intensity PRT. The two sham interventions are educational videos and seated calisthenics. Participants are randomized into 1 of 4 supervised training groups (2 d/wk × 6 mo) in a fully factorial design. Primary outcomes measured at baseline, 6, and 18 months are the Alzheimer's Disease Assessment Scale (ADAS-Cog), neuropsychological test scores, and Bayer Informant Instrumental Activities of Daily Living (B-IADLs). Secondary outcomes are psychological well-being, quality of life, cardiovascular and musculoskeletal function, body composition, insulin resistance, systemic inflammation and anabolic/neurotrophic hormones, and brain morphology and function via Magnetic Resonance Imaging (MRI) and Spectroscopy (fMRS).

**Discussion:**

SMART will provide a novel evaluation of the immediate and long term benefits of CT, PRT, and combined CT and PRT on global cognitive function and brain morphology, as well as potential underlying mechanisms of adaptation in older adults at risk of further cognitive decline.

**Trial Registration:**

Australia and New Zealand Clinical Trials Register (ANZCTR): ANZCTRN12608000489392

## Background

With a forecast 100 million persons with dementia by 2050, this disorder presents a major challenge to sufferers, their caregivers, and the health care system, and delay of disease onset and progression is amongst the most pressing challenges for medical research [1]. A five-year delay in dementia onset and progression could halve disease prevalence [2] and would have a significant impact on disease burden. The efficacy of pharmacological treatments to date have been limited to symptom control [3] and have not been effective in reducing disease onset, and so non-pharmacological preventative interventions are of great interest.

There is strong evidence from cross-sectional and prospective cohort studies that participation in mentally and physically stimulating activities is associated with decreased dementia prevalence and/or incidence [4-9].

Experimental trials indicate that cognitive training can significantly improve performance in healthy adults on a range of cognitive tasks, with an average moderate effect size (ES) of 0.6 [10-13]; and that exercise interventions of as little as one week of aerobic exercise can result in improved memory, attention, and reaction time [14]. Sustained improvements, particularly in executive function, have been shown after aerobic training (ES = 0.41), combined aerobic and resistance training (ES = 0.59), and resistance training alone (ES = 0.53), even after exercise was withdrawn in some cases [15].

Two studies to directly compare single and combined physical and mental exercise found effect sizes across a range of cognitive outcomes to be much larger in the combined condition [12,16]. Both of these studies had design flaws, including very small sample sizes [16] and high dropout rates [12], limiting conclusions. Therefore, a robustly designed trial is required to investigate the comparative benefits of isolated and combined physical and mental training.

The mechanisms of benefit from physical and mental interventions are not clear, it has been postulated that physical and mental activity may therefore have potential to stimulate plasticity of the brain and possibly reduce dementia onset. Animal studies have demonstrated a range of positive neurobiological outcomes, including decreased inflammatory cytokines, decreased cortisol response to stressors, increased insulin-like growth factor-1 (IGF-1) into the brain, increased cerebral blood flow and angiogenesis, and increased hippocampal volume, brain derived neurotrophic factor (BDNF), neurogenesis, and synaptic density after memory-enhancing cognitive and exercise training [7,17]. Human data are more limited, but observations of responses to training have included increased blood flow, aerobic capacity, and region brain volume after behavioural and aerobic training [18,19] and improved brain chemistry using magnetic resonance spectrometry (MRS) in our pilot work with cognitive training [20]. There are fewer human data available on the possible cognitive-enhancing mechanisms of resistance training, with findings of no changes in BDNF [21], and increases in IGF-1 [22]. Animal and human exercise trials indicate that exercise may improve brain function via two pathways; directly through the induction and regulation of growth factors (e.g., BDNF, IGF-1), and/or indirectly via the modulation of systemic inflammation [7]. However, rigorous clinical trials investigating the central and peripheral synergistic benefits of exercise for improved brain function are lacking [7]. Consequently the Study of Mental Activity and Regime Training trial (SMART) was designed and implemented to examine the isolated and combined benefits of cognitive training and resistance training, and to provide novel, comprehensive data on possible proposed links between cognitive improvement and brain and whole-body-adaptation to resistance and cognitive training.

Most cognitive and exercise training trials have targeted healthy, cognitively intact adults. The most vulnerable individuals at highest risk for cognitive decline, however, are those with early cognitive impairment and co-morbid diseases such as cardiovascular disease, type 2 diabetes, obesity, and hypertension (i.e. metabolic syndrome). We are therefore deliberately excluding high functioning volunteers and targeting a highly clinically relevant population, with evidence of early cognitive impairment and various cardiovascular risk factors. These individuals may not be capable of the moderate or high intensity aerobic training that has been shown to be effective in animal and human trials. Resistance training, which has a larger effect size in the literature (0.53) than isolated aerobic training (0.41), and comparable to combined aerobic/resistance training (0.59), may be a more realistic exercise option in this cohort, as it is more feasible in elders with frailty and mobility impairment, thus having the potential for long-term adherence. We [23] and others have shown that resistance training results in many beneficial adaptations in older adults that may be relevant to the mechanisms underlying its putative cognitive benefits. These adaptations (see Figure 1), many of which will be studied in this proposal (particularly changes in fitness, inflammation, and body composition) would not be anticipated after exposure to cognitive training alone, consequently the SMART trial will enable investigation of the efficacy of combining these two distinctly different training paradigms.

**Figure 1 F1:**
[figure not shown]
**Theoretical model of mechanisms linkage between progressive resistance training, cognitive training, and cognitive and functional outcomes**. BDNF = brain-derived neural growth factor IGF-1 = insulin-like growth factor-1.

The SMART trial is a long term study that will measure evidence of both immediate and sustained benefits of training, one year after withdrawal of active treatment. In addition to the selection of general cognitive, functional, physical, mood symptoms and quality of life outcome measures will also be assessed to identify the extent of transfer of benefits of our interventions.

### Objectives and Hypothesis

The primary objective of the SMART trial is *to determine whether cognitive, physical or combined cognitive and physical training can prevent or slow cognitive and functional decline in vulnerable older adults at high risk of dementia*. Our secondary aim is to explore adaptation to these two interventions in the brain, as well as identify potential mechanisms of benefit, in particular modulation of cardiovascular risk profile, systemic inflammatory cytokines, growth factors, fitness levels, and body composition.

#### Primary Hypotheses

1. Six months of supervised cognitive training (CT) will significantly improve cognitive function, as assessed by the Alzheimer's Disease Assessment Scale Cognitive subscale (ADAS-Cog) [24,25], and independence of function as assessed by the Bayer Informant -Activities of Daily Living (BIADL) [26] at both 6- and 18- month follow-up, relative to a sham training control condition.

2. Six months of supervised high intensity progressive resistance training (PRT) will significantly improve cognitive function, as assessed by the ADAS-Cog, and independence of function as assessed by the Bayer Informant -Activities of Daily Living (BIADL), at both 6- and 18-month follow-up, relative to a sham training control condition.

3. The combination of CT and PRT will be significantly superior to either intervention in isolation for cognitive and functional benefits.

#### Secondary Hypotheses

1. All active training interventions will improve brain morphology and biochemistry compared to the sham control condition, as defined by: increased hippocampal volume (mm^3^) by MRI scanning; positive localised Voxel-Based Morphometry (VBM) brain changes (z-score relative change); decreased whole brain volume of White Matter Hyper-intensities (WMHs) (mm^3^); and lead to beneficial hippocampal and posterior cingulate MRS metabolite changes (% increase in N-acetylaspartate, and increase in phosphocreatine metabolites).

2. All active training interventions will improve secondary cognitive outcomes, in the domains of attention, memory, fluency, and executive function, relative to the sham control condition, and combined training will be superior to either single intervention.

3. All active training interventions will maintain global clinical impression scores, as defined by the Clinical Dementia Rating (CDR) scale, relative to the sham control condition.

4. PRT exercise will preferentially decrease inflammatory markers, insulin resistance, and central adiposity and increase fitness (strength and aerobic capacity), muscle mass, and functional mobility, compared to either cognitive or sham control condition.

5. Cognitive and physical training will produce positive effects on psychological health and quality of life above and beyond the non-specific effects seen after sham control condition.

## Methods

### Study Design and Setting

The SMART trial is a longitudinal double-blind, sham training-controlled, randomized clinical trial adhering precisely to CONSORT guidelines http://www.consort-statement.org for the conduct and reporting of clinical trials, as extended to non-pharmacological interventions [27]. Ethical approval was obtained from the Sydney South West Area Health Service (HREC Ref.08/RPAH/106), University of Sydney Human Research Ethics (HREC: 06-2008/11094), University of New South Wales (HREC: 08152), and signed informed consent was obtained from all participants. Participants are from the greater Sydney metropolitan area, and the study is conducted at Cumberland Campus of the University of Sydney in Lidcombe NSW Australia. MRI scans are performed at the Clinical Research Imaging Centre in Randwick NSW Australia.

### Study Population and Eligibility Criteria

Participants are community-dwelling persons aged 55 or above, with primary inclusion criteria being self-reported memory complaint, a Clinical Dementia Rating (CDR) [28] of ≤ 1.0; Mini-Mental Status Examination (MMSE) [29] score of 23-29; and willing to have multiple cognitive, physical and imaging assessments over 18 months. Complete inclusion and exclusion criteria are listed in Table 1.

**Table 1 T1:** Inclusion and exclusion criteria for the SMART trial

Inclusion criteria	Exclusion criteria
Age ≥ 55 Competency in English sufficient for assessment and training Community-dwelling MMSE^ 23-29 CDR^^ ≤ 1.0 TICS ^#^< 30 No unstable disease precluding planned exercise* Absence of significant cognitive decline in 5 years Absence of known organic or psychiatric condition affecting cognition Able to see and hear sufficiently to participate in planned physical and computer-based cognitive training	Unstable medical condition* Participation in any cognitive training activity Participation in > 150 min/wk of moderate or greater intensity planned exercise of any kind Rapidly progressive or terminal illness Pre-existing diagnosis of dementia Psychotic illness (DSM-IV)** Degenerative neurological disorder Diagnosis of stroke or TIA^+ ^within last 12 months, stroke with residual neurological deficit, two or more strokes or TIAs at anytime, One stroke or TIA with residual deficits that preclude participation. TBI ^± ^within past year, or with residual deficits that preclude participation. Diagnosis of depression (DSM-IV) GDS^++ ^>9 or current treatment with antidepressant medications, greater than 3 episodes of depression in the last 5 years ("episode": requiring treatment), > 10 episodes requiring treatment over lifetime, past suicide attempts, current bipolar diagnosis and treatment, > 3 past episodes requiring treatment in last 5 years. Current alcohol or drug abuse (DSM-IV) Unrepaired abdominal or other known aneurysm Myocardial infarction or cardiac surgery within past 6 months NYHA Class IV CHF^±±^ Unstable angina or uncontrolled malignant arrhythmias at rest or on exercise stress testing Recent retinal haemorrhage or detachment/proliferative retinopathy Seizures (>2 in past 12 months)

* Examples of unstable conditions include uncontrolled arrhythmias, hypertension, hyperglycemia, symptomatic enlarging hernia, acute pulmonary embolism, deep venous thrombosis, recent or unstable fracture, inflammatory or traumatic joint injuries, etc. Such individuals may become eligible if medical or surgical treatment stabilizes their condition.

^ MMSE Mini Mental Status Examination ^27^

^^ CDR Clinical Dementia Rating ^26^

^#^TICS Telephone Interview for Cognitive Status -Modified ^30^

**DSM-IV Diagnostic and Statistical Manual of Mental Disorders 4^th ^edition

^+ ^TIA Trans Ischemic Attack

^± ^TBI Traumatic brain Injury

^++ ^GDS Geriatric Depression Scale [49]

^±±^NYHA Class IV CHF New York Heart Association Class IV Class of Heart Failure indicating symptoms evident at rest with any physical activity increasing symptoms, precluding ability to complete physical activity and causing severe limitations.

### Recruitment

Participants are to be recruited from October 2008 until December 2011 from media publicity on state radio, advertisements in local newspapers and businesses, a mail campaign using the electoral roll, contact with participants from previous studies who provided consent for such contact, general practitioner lists, aged care and health service facilities, community programs for seniors and word of mouth.

#### Sample size estimates

Sample size estimates (alpha 0.05, beta 0.20) are based on planned comparisons for the main effects of PRT and CT, as well as the effect of combined training vs. either intervention in isolation on our primary outcome: global cognitive function as assessed by ADAS-Cog. The assumptions are as follows: our meta-analyses [30] and review of published RCTs in older adults [15] reveal Effect Sizes (ES) for a range of cognitive outcomes of approximately 0.60 for cognitive training, 0.59 for aerobic/resistance training, and 0.53 for resistance training, compared to 0.15 for control groups. However, as we are enrolling a cohort with early cognitive impairment, we anticipate a decline of approximately this magnitude (ES = 0.15) over 12 months in our sample, so that the sham control condition would merely offset that decline (ES = 0.0). Thus, we have conservatively powered the study to show an ES of 0.53 for the main effects of both CT and PRT vs. control (n rounded up to 30/group × 4 = 120 required for 4-cell factorial design).

The only two published studies of *combined mental and physical training *[12,16] showed average ES = 0.94 for combined training compared to mental training alone and ES = 1.27 for combined training compared to exercise training alone. Therefore, we have ample power (99.7%) to find a difference of this magnitude between our combined training (n = 30) and isolated training groups (n = 30). Reported dropout from drug trials in MCI is 28% [31] however our experience in fully supervised training of older adults with frailty/chronic disease dropout averages 10-15% over 12 months. Therefore, we will inflate sample size needs for approximately10% drop out rate to account for anticipated attrition (n = 132), and we will recalculate these sample size needs in interim analysis after the first 50 participants have completed 6 months intervention and revise ES and sample size needs if required.

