### Randomisation, concealment, and allocation

A concealed, computer-generated sequence of randomly permuted blocks (block size = 8), stratified by gender and age, is generated by a statistician not otherwise involved in the study (http://www.randomization.com, created by [name], Tufts University). Randomization occurs at the completion of the entire baseline assessment. Where randomization occurs in person, assignments will be placed in sealed opaque envelopes and delivered to subjects by the recruitment officer with subjects designated to 6 months of cognitive training, progressive resistance training, combined cognitive and progressive resistance training, or stretching and video-quiz control group in a 1:1:1:1 ratio. Flow of subjects through the study to date is presented in Figure 3.

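### The planning effect size of 0.53 takes the expected cohort decline off the sham arm only; if the decline applies to all arms, the plan's own figures give contrasts of 0.38 (PRT) and 0.45 (CT)

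*Protocol article*

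**What the plan says.** All of the reasoning is in the protocol article under Sample size estimates. The error rates and the target comparison come first: "Sample size estimates (alpha 0.05, beta 0.20) are based on planned comparisons for the main effects of PRT and CT". The literature effect sizes follow: "approximately 0.60 for cognitive training, 0.59 for aerobic/resistance training, and 0.53 for resistance training, compared to 0.15 for control groups".

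The article then adapts these to a cohort with early impairment: "we anticipate a decline of approximately this magnitude (ES = 0.15) over 12 months in our sample". The consequence is drawn for one arm only: "so that the sham control condition would merely offset that decline (ES = 0.0". The conclusion is: "Thus, we have conservatively powered the study to show an ES of 0.53 for the main effects of both CT and PRT vs. control", with the number given as "n rounded up to 30/group × 4 = 120 required for 4-cell factorial design".

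Two other sections bear on the point. Randomisation, concealment, and allocation assigns participants to the four arms "in a 1:1:1:1 ratio", so all arms come from one cohort. Statistical Analysis plans tests of the CT and PRT main effects and their interaction, in a mixed model adjusted for baseline values.

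**The concern.** The decline is described as a property of the enrolled sample. Randomisation makes the arms alike in expectation, so a decline that belongs to the sample should reach every arm unless training acts on it. The plan subtracts it from sham (0.15 − 0.15 = 0.0) and not from the trained arms, and then uses 0.53 against 0.0 as the contrast. For PRT this moves the contrast from 0.38 to 0.53, in the favourable direction, and the result is called conservative.

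ADAS-Cog is the outcome on which the trial is sized, and the two main effects test the first two primary hypotheses. If the contrast is really 0.38 or 0.45, the stated beta of 0.20 does not follow from the plan's inputs. A non-significant main effect could then be read as stronger evidence of no effect than the design provides.

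**Working it through.** **Inputs from the article.** Effect sizes: CT 0.60, PRT 0.53, control 0.15. Decline 0.15. Alpha 0.05, beta 0.20. Thirty per cell, equal allocation, so each main effect compares 60 with 60.

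**Assumptions.** Effect sizes are in SD units (SD = 1). The test is two-sided; the article does not say so, but a one-sided test would need only 45 per margin (23 per cell), which does not lead to 30. There is no CT × PRT interaction on the margins.

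**1. The plan's own number.** Normal approximation: n per margin = 2(1.960 + 0.842)² / d². With d = 0.53 this is 15.70 / 0.2809 = 55.9, so 56; the t-test gives 57. That is 28 to 29 per cell, which rounds up to 30. Power at 60 versus 60 is 82.1% (t-test; the two-way ANOVA F test agrees). The stated size follows correctly from 0.53.

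**2. The contrast with the decline in every arm.**
- PRT: (0.53 − 0.15) − (0.15 − 0.15) = 0.38
- CT: (0.60 − 0.15) − (0.15 − 0.15) = 0.45

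These equal the literature differences 0.53 − 0.15 and 0.60 − 0.15, because a common decline cancels.

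**3. The contrast if training fully prevents the decline.** PRT: 0.53 − 0.0 = 0.53. CT: 0.60 − 0.0 = 0.60. For PRT, 0.53 is therefore the top of the range. For CT, 0.53 needs 0.53 − 0.45 = 0.08 of the 0.15 to be prevented, a little over half.

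**4. Unadjusted power, t-test, two-sided 0.05.**

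| Contrast | Power, 60 v 60 | Needed per margin for 80% |
|---|---|---|
| 0.53 | 82% | 57 |
| 0.45 (CT, net) | 69% | 79 |
| 0.38 (PRT, net) | 54% | 110 |

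As a check by the normal approximation, 0.38 × √30 = 2.081, and Φ(2.081 − 1.960) = 0.548. With 132 randomised and 10% lost (about 59 per margin), power is 54% for PRT and 68% for CT. With all 132 analysed it is 58% and 73%. The minimum detectable main effect at 80% power with 60 versus 60 is about 0.52.

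**5. With baseline adjustment.** If the effect sizes are in raw-score SD units, adjusting for a baseline with correlation r to follow-up changes the effective d to d / √(1 − r²). The article gives no r; 0.5 and 0.7 are assumed here.

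| r (assumed) | PRT: effective d, power | CT: effective d, power |
|---|---|---|
| 0.5 | 0.38 / 0.866 = 0.44, 66% | 0.45 / 0.866 = 0.52, 81% |
| 0.7 | 0.38 / 0.714 = 0.53, 82% | 0.45 / 0.714 = 0.63, 93% |

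Eighty percent is reached at r of about 0.68 for PRT and 0.49 for CT.

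**The case against.** Several points on the other side have weight.

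- **Within-group or between-group.** The article never says that 0.53 and 0.60 are arm-specific changes, and the cited sources are not available here. The arm-specific reading is an inference, but the likelier one: setting a control figure of 0.15 beside them and then moving sham to zero would serve no purpose if the effects were already net of control.
- **Training may act on the decline.** Objectives and Hypothesis asks whether training can prevent or slow decline. If it fully did, the trained arms would not lose the 0.15. This is a coherent position, and it makes 0.38 and 0.45 the lower ends of ranges. The sample-size section does not state it, and it assumes part of what the trial is meant to show.
- **Baseline adjustment.** The planned model may recover much or all of the power, as shown above. This stands as a possibility, but the printed 30 per cell is reproduced without it.
- **The planned recalculation.** The same section commits to revising the effect size and sample size once 50 participants have completed 6 months. That limits the consequence without making the printed justification right. The Results section keeps the recruitment target on retention alone.
- **The word 'conservatively'.** 0.53 is the lowest of the three active figures and is applied to CT in place of 0.60. That gives the word some basis, but 0.53 still exceeds the net 0.45.

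A reader might also think that the 12-month horizon of the decline, which matches neither the 6- nor the 18-month assessment, weakens the power further. It does not bear on this result: a decline common to all arms cancels whatever its horizon.

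**Conclusion.** The point holds as an unsupported planning assumption. The article applies a cohort-wide decline to one arm, gives no reason, and calls the resulting contrast conservative. On its own inputs the contrast is 0.38 for PRT and 0.45 for CT if the decline is equal in all arms, with unadjusted power of about 54% and 69%. It reaches 0.53 for PRT only if training fully prevents the decline. This rests on the arm-specific reading of the effect sizes, a two-sided test and no interaction on the margins.

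A reader might infer that the trial's power simply is 54% and 69%, or that the sample-size arithmetic is wrong. The document supports neither. The arithmetic from 0.53 to 30 per cell is sound; the input is at fault. The unadjusted figures also do not describe the planned baseline-adjusted analysis, whose power cannot be fixed without a correlation that the article does not give. What can be said is that the stated beta of 0.20 is not supported by the inputs and calculation shown.

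**What to change.** In Sample size estimates:

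1. Delete 'conservatively'.
2. State the net between-arm effects, 0.38 (PRT) and 0.45 (CT). Alternatively, keep 0.53 and state openly the assumption behind it: that training fully offsets the expected decline for PRT, and a little over half of it for CT.
3. Restate the power of 30 per cell as about 54% (PRT) and 69% (CT) unadjusted, with the range under the planned baseline adjustment and the assumed correlations shown. Or state about 0.52 as the minimum detectable main effect at 80% unadjusted power.
4. Use the net effect in the recalculation after the first 50 participants, and take the baseline-to-follow-up correlation from blinded pooled data at that point.

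The cost is a rewritten paragraph and a less favourable stated power. No extra enrolment is asked for, and the design and analysis model stay as they are.

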### Blinding

Subjects are informed that they will be randomly assigned to one of four treatment groups by the recruitment officer, and will be blinded to the investigators' hypothesis as to which is the preferred intervention arm. All groups will have an equal volume and frequency of contact with trainers over the 18 months of the study. All primary and secondary outcomes will be obtained and analyzed by blinded assessors on different days to the training programs.

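### The interim look is to revise the effect size from the first 50 participants and, if required, reset N from it, but a between-arm estimate that imprecise is a poor guide to sample size

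*Protocol article*

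**What the plan says.** The section on sample size estimates in the protocol article states that "Sample size estimates (alpha 0.05, beta 0.20) are based on planned comparisons". These are the main effects of CT and PRT, and combined against single training, on ADAS-Cog. The trial is "conservatively powered the study to show an ES of 0.53 for the main effects of both CT and PRT vs. control", with "n rounded up to 30/group × 4 = 120 required for 4-cell factorial design", inflated to 132 for about 10% dropout.

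The same section then plans an interim review: "we will recalculate these sample size needs in interim analysis after the first 50 participants have completed 6 months intervention and revise ES". The full clause reads "revise ES and sample size needs if required", so a change is conditional.

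The Blinding section says "All primary and secondary outcomes will be obtained and analyzed by blinded assessors". It does not say who would receive interim effect estimates. The Statistical Analysis section plans a mixed model, adjusted for baseline, that tests both main effects and their interaction; it does not mention the interim review. The Results section reports a later check of the recruitment target based on retention alone (120/0.90 = 133).

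**The concern.** In the sample size section, the effect size is a contrast between arms in SD units. The article gives no ADAS-Cog difference in points and no SD. Revising the effect size from trial data therefore appears to need a comparison of arms on the primary outcome, and N could then follow from that comparison. Coded arm labels would not change this.

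Three things are at stake:

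- **Precision.** Fifty participants may say too little about the effect to guide N.
- **Type I error.** If N depends on the interim effect and the pooled data are then tested in the ordinary way, the error rate exceeds its nominal level.
- **Masking.** Interim effects could reach people running the trial while recruitment, training and the 6- and 18-month assessments continue.

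**Working it through.** **Inputs.** Sample size section: alpha 0.05, power 0.80, effect size 0.53, 30 per cell, 132 after inflation, review at 50 participants. Randomisation section: 1:1:1:1 allocation. Assumptions: two-sided tests, because sidedness is not stated, and a normal approximation.

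**The plan's own figure.** n per side = 2(1.960 + 0.842)² / 0.53² = 55.9, so 56 against 56, or 112 in total (28 per cell). The article rounds up to 30 per cell, or 120, where power is 82.7%. Then 120 × 1.10 = 132. The plan's figure is reproduced. One-sided testing would need 45 per side and does not fit.

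**Precision at the review.** Fifty participants give about 25 against 25 for each main effect.

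- SE(ES) = √(2/25) = 0.283, and the 95% half-width is 1.96 × 0.283 = 0.55, slightly more than the design effect.
- If the true value is 0.53, the 95% range of the interim estimate is −0.02 to 1.08.
- P(estimate < 0.30) = Φ(−0.23/0.283) = 21%. P(estimate > 0.80) = 1 − Φ(0.27/0.283) = 17%.
- For combined against single training, about 12.5 against 12.5: SE = √(2/12.5) = 0.40.

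**Implied N.** Total N = 4(1.960 + 0.842)² / ES² = 31.4 / ES². With a true effect of 0.53:

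| Percentile of interim ES | Interim ES | Implied total N |
|---|---|---|
| 25th | 0.339 | 273 |
| 50th | 0.530 | 112 |
| 75th | 0.721 | 60 |

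The implied N lies within 25% of 120 (90 to 150) in only 19% of trials. It exceeds 240 in 28%, and it is 50 or fewer in 18%.

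**With baseline adjustment.** The article gives no correlation; assume 0.7. Then SE = 0.283 × √(1 − 0.49) = 0.202. Putting the same reduction into the N formula gives 31.4 × 0.51 / ES² = 16.0 / ES², with median 57. The interquartile range is about 36 to 103, and the 5th to 95th percentile estimates imply about 410 down to 22.

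**Type I error, if the final test is unadjusted.** This was simulated under no effect. N is reset to 31.4 / ES² at the interim, limited by a floor and a cap, and all data are pooled and tested at two-sided 0.05. The article gives no rule, so the floors, the caps (total N of 200, 264, 400 and 800) and the handling of an estimate favouring sham are all assumptions. Each range runs from the lowest to the highest cap, with 2,000,000 runs per setting.

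| If the interim estimate favours sham | N can only rise from 132 | N can also fall to 50 |
|---|---|---|
| N goes to the cap, or stays at 132 | 5.3 to 5.8% | 5.9 to 6.4% |
| N is set from the size of the estimate, ignoring sign | 5.5 to 6.5% | 6.8 to 7.8% |

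**The case against.** The strongest reply is that this is a condensed article. Alpha handling, the re-estimation rule and access to interim results commonly sit in an analysis plan that is not shown. That stands. A reader might infer that the trial has no alpha protection, but the article is only silent. The 0.05 it gives belongs to the sample size calculation, and no level is stated for the final test.

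A reader might also infer that the investigators will see results by arm. No section says so. Outcomes are to be analysed by blinded assessors, and release of interim effects is a risk, not a stated fact.

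Nor does the article show that an effect-based change was made. The clause says if required, and the Results section reports only a retention check.

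The type I inflation is modest and rests on assumed rules. With N only rising to a cap of 200 and directional handling of the estimate, it is about 5.3%. The higher caps look remote: the article reports under 4% of contacts recruited and 80 participants enrolled so far. A fall to 50 is equally remote, with 80 already enrolled. The unadjusted standard error of 0.28 is also pessimistic, since the planned model adjusts for baseline.

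None of this removes the core point. The trigger, the quantity to be revised and the possible consequence for N are all in the text. An analysis plan could control alpha and access, but it could not make 50 participants informative about the effect size.

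**Conclusion.** The point holds as a should-fix. The article plans to revise a between-arm effect size from 50 participants and, if required, to reset N from it. Imprecision is the main ground: with 0.53 exactly true, the implied N has an interquartile range of about 60 to 273 unadjusted, and remains widely spread under an assumed correlation of 0.7. A correctly planned trial could be resized by chance alone.

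Type I inflation is secondary and conditional. It is roughly 5.3 to 6.5% if N can only rise and 5.9 to 7.8% if it can also fall, provided the final test is unadjusted and the assumed rules apply. The documents do not support stating as fact that alpha is uncontrolled, that masking is broken, or that N has already been changed on an interim effect.

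**What to change.** - Remove the commitment to revise the effect size. Hold the design value at 0.53 and state that N will not fall below the planned figure.
- Limit the review to blinded nuisance parameters: dropout, and the pooled correlation between baseline and 6 months. Dropout is the one that can raise N: at the 28% the article cites from drug trials, 120/0.72 = 167. The 120 was computed without baseline adjustment, so the correlation can only show how much power is in hand.
- Use the pooled SD only if a target difference in ADAS-Cog points is stated first. While the design effect is purely standardised, the SD cannot change N. On about 46 degrees of freedom the SD has a 95% interval of 0.83 to 1.26 times its value, so N would vary by 0.69 to 1.58 times (112 becomes about 77 to 177). The no-decrease rule would cut off the lower part.
- If an effect-based revision has been or will be made, disclose it, restrict access to an independent statistician, and use a combination test in the final analysis.

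The main change is a short amendment, and the blinded review is less work than a comparison of arms. Using the SD would need one new design figure. The real cost is that the sponsor gives up revising the effect size mid-trial: if the true effect is smaller than 0.53, the trial will not be enlarged to detect it.
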